### Evaluation of the Efficacy

#### Justification of Analysis

The study design for evaluating the tool will be a stepped wedge, randomized controlled trial. In this design, an intervention is launched sequentially to clusters over a number of time periods. This design is characterized by the fact that clusters are randomized for the time at which the cluster will switch from the control condition to the intervention condition. Stepped wedge designs incorporate data collection at each point (step) where a new group receives the intervention [46]. The period with no intervention is used as the control, which allows the study to take into account independent variables that might affect screening rate (such as migration changes or behavior changes brought on by the COVID-19 pandemic). This pragmatic design enables evaluations of how interventions would work in a real-world setting with limited exclusion criteria [64]. The other reason for choosing a stepped wedge cluster is ethics; it could be unethical or politically controversial to withhold an intervention that is deemed more effective than harmful to a control cluster [47]. The stepped wedge methodology is often used in public health research projects, especially in the field of HIV [47].

#### Setting

The study will be carried out in 16 centers taking care of and treating migrants, including the provision of screening tests: immigration centers (OFII), hospital consultations specialized for underserved persons (PASS), nonprofit organizations offering rapid tests to migrants (not exclusively), ambulatory health care professionals (general practitioners, gynecologists, midwives) with large migrant patient populations. Different regions of France will be represented.

#### Inclusion and Exclusion Criteria

For participating centers, the inclusion criteria are as follows. For the types of settings, OFII centers having participated in the STRADA study, PASS hospital services, medical doctors or midwives, and organizations accredited to conduct HIV and hepatitis B and C rapid tests will be used. Regarding the level of experience of the centers, we will require that they be consulting with a significant number of migrants (≥500 the previous year), experienced in offering those screening tests to migrants, and experienced in orienting patients with a positive result to an appropriate hospital service and in orienting patients to other support services if needed. Centers must also have the following resources and organization: have sufficient resources to get a phone interpreter or solution in case of a positive result and sufficient privacy to conduct a test with the assistance of an audio app.

For individual participants (migrants), the inclusion criteria are migrant status (born outside of France), over 18 years of age, having a low level of proficiency in French (not able to follow the consultation alone), not speaking another language in common with the health professional, and fluently speaking a language available in the app. The exclusion criteria are being French, speaking French, or not able to understand any of the languages available in the tool.

#### Intervention and Control

The control period will correspond to the typical processes of these centers for screening migrants (use of phone or in-person interpreters, informal interpreters, or not offering screening tests to migrants because of the language barrier). The intervention will be the use of the app during consultations with non-French speaking migrants to offer, explain, and carry out the screening test, with the possible help from professional interpreters if necessary.

#### Outcomes

The primary outcome measured is the percentage of screening tests administered. The secondary outcomes are rate of screening proposals by health professionals or associate workers, acceptance rate by migrants, number of positive cases during screening using this app, and frequency of use of the app.

#### Sample Size

The overall rate of screening currently carried out as part of the STRADA study in OFII centers is around 45% (average of 2 years, taking into account health professionals not offering a test and migrants refusing when the screening is offered). The primary hypothesis of this study is that the addition of the electronic screening app will increase this rate by 10%, from 45% to 55% (including an increase in the rate of screening offered by health professionals and a decrease in the refusal rate among migrants to whom screening is offered). With an alpha risk of 0.05 and a beta risk of 0.20, the total number of subjects required is 778 (ie, a workforce of 900 participants to be included to take account for missing data). Statistical comparisons will be made at the threshold of *P*<.05.

A moderate improvement was chosen because it would be a realistic but meaningful improvement, whereas a small effect size would be too small for clinical significance. Thus, our sample size will allow for the detection of moderate improvements, with ample data for subgroup analyses as well.

We will do a simple and pragmatic step wedge with 2 groups and 3 steps: first step without intervention, second starting intervention for 1 group (half of the centers), and third all centers with the intervention [65,66]. We plan to have 2 clusters with 450 participants in the OFII centers and 450 participants in the other structures (PASS, associated structures). Power and sensibility fit sample size and step wedge configuration were checked with the design effect method [67,68].

Subgroup analyses will be performed based on several variables (screening structure, level of health literacy, geographic origin of migrant, level of education, gender, age group) without adjusting the significance threshold.

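### The required N of 778 is the individually randomised two-arm figure; under a step-adjusted analysis of the planned 2-group, 3-step wedge, power for a 10-point gain is well below the stated 80%

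*Protocol article*

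**What the plan says.** All of the sample-size reasoning is in the Sample Size section of the protocol article.

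- **Effect:** the app "will increase this rate by 10%, from 45% to 55"%.
- **Error rates and N:** "With an alpha risk of 0.05 and a beta risk of 0.20, the total number of subjects required is 778".
- **Enrolment:** "a workforce of 900 participants to be included to take account for missing data". No other reason for inflation is given.
- **Design:** "We will do a simple and pragmatic step wedge with 2 groups and 3 steps". The first step has no intervention, the "second starting intervention for 1 group (half of the centers), and third all centers with the intervention".
- **Check:** "Power and sensibility fit sample size and step wedge configuration were checked with the design effect method". No ICC, design effect, or resulting N or power is shown.

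The Setting section gives 16 centres. The Sample Size section speaks of two clusters of 450, one for the immigration centres and one for the other structures. Justification of Analysis says the control period lets the study take account of influences on the screening rate such as migration changes or COVID-19 behaviour. Statistical Analysis names a mixed model for the stepped wedge.

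**The concern.** The N of 778 matches a design that the trial does not use. In the planned wedge, step 1 is all control and step 3 is all app. Once step is in the model, those two steps carry no direct comparison of conditions, and with no clustering all the information comes from step 2. An N that ignores this overstates power for the primary outcome.

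If power is well below 80%, a true 10-point gain would more likely be missed than found, and a null result could be read as showing that the app does not work. The same section also relies on this N when it says there will be enough data for subgroup analyses.

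**Working it through.** **1. Reproducing 778.** Inputs from Sample Size: p0 = 0.45, p1 = 0.55, alpha 0.05, power 0.80. Sidedness is not stated; two-sided is the choice that reproduces the figure.

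n per arm = (1.960 + 0.842)² x (0.45 x 0.55 + 0.55 x 0.45) / 0.10² = 388.5, so 389, and 2 x 389 = 778. The match is exact: design effect 1.00. (The pooled-variance version gives 784; one-sided versions give 614 to 618.) Enrolling 900 to analyse 778 allows for 1 - 778/900 = 13.6% missing.

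**2. The wedge at ICC 0, by hand.** Assume three equal steps. With step effects, only step 2 compares conditions, and it holds N/3 patients, N/6 per condition. Variance per patient = 0.45 x 0.55 = 0.2475.

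- N = 778: SE = √(2 x 0.2475 / 129.7) = 0.0618; power = Φ(0.10/0.0618 - 1.960) = 37%.
- N = 900: SE = √(2 x 0.2475 / 150) = 0.0574; power = 41%.

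The required total is 3 x 778 = 2,334, before any clustering.

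**3. The wedge with clustering.** Generalised least squares with fixed step effects and a random centre effect: 16 equal centres, eight with pattern 0/1/1 and eight with 0/0/1, m = N/48 patients per centre-step (16.2 at 778; 18.75 at 900). Var(effect) is the treatment element of [Σ X′V⁻¹X]⁻¹, where V has ICC x 0.2475 in every cell plus (1 - ICC) x 0.2475/m on the diagonal. Power = Φ(0.10/SE - 1.960); detectable difference at 80% power = 2.802 x SE. The ICC values are assumptions.

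| ICC | Power, 778 | Detectable, 778 | Power, 900 | Detectable, 900 | Total N for 80% |
|---|---|---|---|---|---|
| 0 | 36.6% | 17.3 pts | 41.3% | 16.1 pts | about 2,340 |
| 0.01 | 33.5% | 18.3 | 37.5% | 17.1 | about 2,950 |
| 0.02 | 32.0% | 18.8 | 35.7% | 17.6 | about 3,120 |
| 0.05 | 30.4% | 19.3 | 34.0% | 18.1 | about 3,190 |
| 0.10 | 30.4% | 19.4 | 34.1% | 18.1 | about 3,080 |

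**4. Sensitivity.**

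- *Correlation decaying over time* (cluster autocorrelation 0.8): at 778, 27.5% (ICC 0.05) and 24.3% (ICC 0.10); at 900, 30.2% and 26.3%.
- *Unequal steps, 50-60% of patients in step 2, constant correlation:* about 36-58% at 778 and 40-65% at 900, over ICC 0 to 0.10. Even with 80% of patients in step 2, power at 900 is 77% at ICC 0 and 35% at ICC 0.10.
- *Two clusters taken literally, constant correlation:* about 28-34% at 778 for ICC 0.001 to 0.10.
- *No step effects in the model, equal steps, 16 centres, constant correlation:* 79-80% at 778 and 84-86% at 900, over ICC 0 to 0.10.

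**The case against.** **The model is partly assumed.** The article gives no step sizes and no ICC, and Statistical Analysis does not name step effects. The fall from 80% to 37% at ICC 0 with 778 analysed comes entirely from step adjustment. This stands as a limit on precision: a reader might infer that the trial's power simply is 30-41%, but the documents do not support that. Such a range also mixes 778 and 900 analysed, is not a floor if correlation decays, and is not a ceiling if step 2 is large. The direction is not in doubt. Justification of Analysis presents the design as a way to account for changes over time, and without step effects those changes would be confounded with the app. No step-adjusted configuration examined reached 80%.

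**A design-effect check is reported.** A reader might infer that it was not done. The documents do not show that, because its sources and the full protocol are not at hand. They do show that it left no trace in N: 778 is uninflated and 900 is explained by missing data alone. Nor is the absence of an ICC from a condensed article the fault here; the fault is a stated N that does not fit the stated design.

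**The 80% is attached to 778, not 900.** This is correct. The plan does not say that 900 gives 80% power, and the correction should be framed for 778 analysed out of 900 enrolled.

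**The arithmetic is right.** It is. The formula belongs to another design.

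**Conclusion.** The point holds in conditional form. The plan presents an individually randomised N as the requirement for a stepped wedge, with no visible allowance for clustering or step adjustment.

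With step effects, 16 equal centres, three equal steps, ICC 0 to 0.10 and constant correlation, power with 778 analysed is about 30-37%, not 80%, and the detectable difference is about 17-19 points, not 10. If all 900 were analysed, the figures are 34-41% and about 16-18 points. The threefold shortfall at ICC 0 does not depend on a guessed ICC, but it does depend on equal steps and on adjusting for step. The exact values cannot be settled until the number of clusters and the step sizes are fixed. The statement of power for the primary outcome should not stand as written.

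**What to change.** 1. First reconcile the 16 centres in Setting with the two clusters in Sample Size, because the recalculation depends on it.
2. Replace the 80% power statement with the power and detectable difference for 778 analysed (900 enrolled) under the step-adjusted stepped-wedge model. State the assumed ICC, cluster autocorrelation and step sizes, each with a range.
3. Report the inputs and result of the design-effect check, or correct that sentence.
4. Withdraw the statement that this N leaves ample data for subgroup analyses.

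**Cost:** a recalculation and a rewritten paragraph. The stated power becomes less favourable. Correcting the statement needs no extra patients. If the sponsor instead wants 80% power for 10 points, the total under the equal-step assumptions above is about 2,340 to 3,190 analysed patients, and more if the correlation decays over time.

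### The sample size is said to leave plenty of data for six subgroup analyses, but it is the minimum for the overall comparison and gives at best about 57% power in half the sample

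*Protocol article*

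**What the plan says.** Everything on this point is in the Sample Size section of the Protocol article, under Evaluation of the Efficacy.

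- Control rate: "The overall rate of screening currently carried out as part of the STRADA study in OFII centers is around 45" per cent.
- Target: the app "will increase this rate by 10%, from 45% to 55" per cent.
- Size: "With an alpha risk of 0.05 and a beta risk of 0.20, the total number of subjects required is 778", then "a workforce of 900 participants to be included to take account for missing data".
- Adequacy claim: "Thus, our sample size will allow for the detection of moderate improvements, with ample data for subgroup analyses as well".
- Subgroup variables and error control: "screening structure, level of health literacy, geographic origin of migrant, level of education, gender, age group) without adjusting the significance threshold".
- Design: "We will do a simple and pragmatic step wedge with 2 groups and 3 steps". The 900 are split into 450 from OFII centres and 450 from other structures.

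The section adds that the configuration was checked by a design effect method. It gives no intracluster correlation, design effect or resulting power, and no power for any subgroup. The subgroup analyses are not described as exploratory.

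**The concern.** The claim concerns a property of the design, so it can be tested against the figures that precede it. A sample sized for 80% power on one overall comparison has no reserve: any subset has less power for the same effect, and a difference in effect between subsets is harder still to detect. Geographic origin, literacy, education and age group can each have more than two levels, so many subgroups would hold fewer than 450 people.

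Interpretation is at stake. A reader told that data are plentiful will take a non-significant subgroup as evidence that the app does not work there, when low power is the likelier reason. The same reader will give a significant subgroup more weight than one of six unadjusted tests deserves.

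**Working it through.** **Inputs from the plan.** p1 = 0.45, p2 = 0.55, difference 0.10, alpha 0.05 (two-sided, which reproduces the stated number), power 0.80, N = 900, 16 centres (Setting), two sequences and three periods. Variance per observation is 0.45 x 0.55 = 0.2475 in both arms.

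**Step 1. Reproduce 778.** Per arm, n = (1.96 + 0.8416)^2 x (0.2475 + 0.2475) / 0.10^2 = 388.5, rounded up to 389. Two arms give 778, the stated figure. It therefore contains no inflation for clustering, for the stepped wedge or for subgroups. The increase to 900 is 122 people, 122/900 = 13.6%, which the plan assigns to missing data.

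**Step 2. Most favourable case: no clustering, no period effects, nobody missing.** With half of a subgroup of size n in each condition, SE = sqrt(2 x 0.2475 / (n/2)) and power = Phi(0.10/SE - 1.96).

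| Group | SE | 0.10/SE | Power |
|---|---|---|---|
| All 900 | 0.0332 | 3.015 | 85% |
| 450 | 0.0469 | 2.132 | 57% |
| 300 | 0.0574 | 1.741 | 41% |
| 225 | 0.0663 | 1.508 | 33% |

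For a 10-point interaction between two halves of 900, SE = sqrt(4 x 0.2475 / 225) = 0.0663, so power is 33%. If only 778 are analysed, as the plan allows for, a half has 389 people, 194.5 per condition: SE = 0.0504, power 51%. The interaction falls to 29%.

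**Step 3. The planned stepped wedge with period effects.** The plan gives no intracluster correlation (ICC), so 0 to 0.10 is assumed, with cluster autocorrelation 1. The variance of the treatment effect is the last diagonal element of the inverse of the sum over centres of Z'V^-1 Z. Z holds three period indicators and the treatment indicator, with sequences (0,1,1) and (0,0,1); V is the covariance of a centre's three period means.

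The ICC = 0 case can be done by hand. Only the second period contains both conditions, so a subgroup of 450 contributes 150 people, 75 per condition: SE = sqrt(2 x 0.2475 / 75) = 0.0812, and power = Phi(1.231 - 1.96) = 23%.

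Over ICC 0 to 0.10:

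- Subgroup of 450 spread over all 16 centres: 20-23%, with a detectable difference of 23-25 points.
- Subgroup of 450 confined to 8 centres: 19-23%. This fits the OFII/other split better, but 8 is an assumption because the article does not give the number of OFII centres.
- With cluster autocorrelation 0.8, the lowest values are 18% (16 centres) and 15% (8 centres).

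**Step 4. Interaction in the stepped wedge.** For a variable that splits each centre evenly, fitted in one model on all 900, a 10-point interaction has 33% power at ICC 0 and 36% at ICC 0.10 if the subgroups share period effects. If each subgroup has its own period effects, power is 14-15%.

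**Step 5. Multiplicity.** Six independent tests at 0.05, all nulls true: 1 - 0.95^6 = 26.5% chance of at least one false positive.

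**The case against.** The strongest reply is that the plan makes no subgroup claim. It has one primary outcome and one primary hypothesis, it states openly that the subgroup threshold is unadjusted, and an exploratory label or a method for testing interactions often sits in a fuller document. All of that stands, and unadjusted exploratory subgroup analyses are ordinary practice. It does not rescue the adequacy statement, which the article itself makes and no other document could make true.

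A second reply is that the design effect check may have settled the matter. The sources cited for it are not available here, but 778 is the uninflated number, so whatever was checked did not change the size.

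Four stronger readings are tempting, and the documents do not carry them.

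- *That 900 is too few even for the main effect.* This is a separate sample-size question. It depends on 900 being the total over all steps and on period terms in the model, which the Justification of Analysis section implies but the Statistical Analysis section does not spell out. Without period terms, main-effect power at 900 is about 72-86%; with them, 26-41% (ICC 0 to 0.10, autocorrelation 1 or 0.8). The subgroup point needs neither assumption.
- *That interaction power is only 12-14% throughout.* That comes from treating each subgroup as its own stepped-wedge trial. In one model with shared period effects, a variable that varies within centres has 33-36%.
- *That a chance subgroup finding would steer deployment.* The Discussion links further development to a demonstrated increase in screening rates and acceptability, not to any subgroup result.
- *That the false-positive risk is 26%.* This needs six independent true nulls. The variables are measured on the same people, and some, such as literacy and education, are probably correlated. It is illustrative only.

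**Conclusion.** The concern holds for the adequacy statement. In the most favourable case, which uses only the plan's inputs and even splits, no subgroup of half the sample or less exceeds about 57% power for the planned effect, and a 10-point interaction has 33%. With period effects in the stepped wedge and an assumed ICC of 0 to 0.10, the half-sample figure is about 19-23% and the interaction 33-36% or 14-15%, depending on whether period effects are shared. If 900 were read as the number per step (2,700 in total), a half-sample subgroup would still have only 32-57%, so the conclusion survives that reading too.

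The absence of a multiplicity adjustment is not an error in itself. The fault is pairing unadjusted tests with a statement that the data are sufficient for them. The primary analysis is unaffected.

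**What to change.** In the Sample Size section:

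1. Delete the part of the adequacy sentence after the comma.
2. State that the six subgroup analyses are exploratory and that the trial is not powered for them.
3. Report each as a treatment-by-subgroup interaction estimate with a 95% confidence interval from the primary mixed model, without claims of significance within subgroups. Say whether period effects are shared across subgroups, because precision depends heavily on it.

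With these changes the unadjusted threshold can stay. A formal correction such as Holm across the six interactions is optional, and would matter only if a P value were meant to support a claim. The change is to wording and reporting and adds no participants. Its cost is a less favourable statement about what the trial can say on subgroups.

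### App and usual care run side by side only in step 2 of the two-group, three-step layout, and giving that step about half of the enrolment would recover some power at little cost

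*Protocol article*

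**What the plan says.** Sample Size (Protocol article) fixes the layout: "We will do a simple and pragmatic step wedge with 2 groups and 3 steps", described as "first step without intervention, second starting intervention for 1 group (half of the centers), and third all centers with the intervention". Setting gives the number of centres: "The study will be carried out in 16 centers". The target is to "increase this rate by 10%, from 45% to 55" per cent. On size, the text reads "With an alpha risk of 0.05 and a beta risk of 0.20, the total number of subjects required is 778", with "a workforce of 900 participants to be included to take account for missing data". It adds that "Power and sensibility fit sample size and step wedge configuration were checked with the design effect method", but shows no intracluster correlation, design effect or number of patients per step.

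The same section splits enrolment into 450 participants in OFII centres and 450 in other structures, and calls these two clusters. Justification of Analysis says the control period lets the study account for influences that vary over time, with migration and COVID-19 behaviour as examples. Statistical Analysis names a mixed-effects model suited to a stepped wedge.

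**The concern.** A stepped wedge chosen to handle changes over time has to be analysed with step in the model. Once it is, a step in which all centres are in the same condition says nothing directly about the app. Its data help only by showing how the two groups of centres differ when treated alike, so that this difference can be removed from the step 2 comparison.

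With only two switch dates there is exactly one mixed step. The share of patients placed in it therefore largely determines how much the trial can learn, and the protocol does not say what that share is. If it is a third, a real 10-point gain in screening would more likely be missed than found.

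**Working it through.** **Inputs.** From the protocol: 45% and 55%, alpha 0.05, beta 0.20, 778 required and 900 enrolled, 16 centres (8 per group), three steps. Assumed: two-sided test, fixed step effects, equal centre sizes, ICC (ρ) 0.01 to 0.20, cluster autocorrelation (CAC) 1 or 0.8, full effect at the switch, normal test, σ² = 0.45 × 0.55 = 0.2475.

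**1. The stated figure.** Per arm: (1.960 + 0.842)² × (0.2475 + 0.2475) / 0.10² = 388.5, so 389, and 2 × 389 = 778. This is the size of an individually randomised two-arm trial, with no allowance for centres or steps.

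**2. Variance in this layout.** Let D1, D2, D3 be the differences in mean screening rate between the two groups in each step. D1 and D3 contain only the chance difference between the groups of centres. D2 contains that difference plus the app effect. With m_t patients per centre in step t:

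- v_t = [σ²(1−ρ)/m_t + σ²ρ(1−CAC)] / 4
- B = σ²ρ·CAC / 4
- Var(effect) = v_2 + 1 / (1/B + 1/v_1 + 1/v_3)

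The first term depends only on step 2. Steps 1 and 3 enter only the second term.

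**3. Worked case, ρ = 0.05, CAC = 1.** B = 0.2475 × 0.05 / 4 = 0.00309 and σ²(1−ρ) = 0.2351.

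- Equal steps (300/300/300; m = 18.75): v = 0.2351/75 = 0.003135. Var = 0.003135 + 1/(323.2 + 638.0) = 0.004175, SE 0.0646, z = 1.548, power = Φ(1.548 − 1.960) = 34%.
- 225/450/225 (m = 14.06, 28.13, 14.06): v_2 = 0.2351/112.5 = 0.002090, v_1 = v_3 = 0.004180. Var = 0.002090 + 1/(323.2 + 478.5) = 0.003337, SE 0.0578, z = 1.731, power = Φ(1.731 − 1.960) = 41%.

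Check at ρ near 0: only step 2 counts, so Var = 4 × 0.2475/300 = 0.0033 and power is 41%, the same as a plain comparison of 150 with 150.

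**4. Power (%), 900 patients, 16 centres.** The last layout uses the general least-squares form of the same model.

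| Layout | CAC | ρ≈0 | 0.01 | 0.05 | 0.10 | 0.20 |
|---|---|---|---|---|---|---|
| 2 groups, equal steps | 1 | 41.3 | 37.5 | 34.0 | 34.1 | 36.5 |
| 2 groups, 225/450/225 | 1 | 56.7 | 49.2 | 40.9 | 39.6 | 41.3 |
| 4 groups, 5 equal steps | 1 | 56.7 | 50.9 | 44.9 | 44.4 | 47.1 |
| 2 groups, equal steps | 0.8 | 41.3 | 37.0 | 30.2 | 26.3 | 21.9 |
| 2 groups, 225/450/225 | 0.8 | 56.7 | 48.5 | 35.8 | 29.6 | 23.5 |
| 4 groups, 5 equal steps | 0.8 | 56.7 | 51.0 | 42.3 | 38.1 | 33.6 |

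Gain from 225/450/225 over equal steps at ρ 0.01 to 0.10: from 29.6 − 26.3 = 3.3 up to 49.2 − 37.5 = 11.7 points. At ρ = 0.20: 41.3 − 36.5 = 4.8 points (CAC 1) and 23.5 − 21.9 = 1.6 points (CAC 0.8).

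**5. Delayed uptake (illustrative; no delay is documented).** The app is given no effect for a fixed share of trial time after each switch, with CAC 1 and ρ = 0.01/0.05/0.10:

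- Delay 10%: equal steps 19.0/15.1/14.4; 225/450/225 31.0/21.7/19.5; 4 groups × 5 steps 25.0/18.1/16.5.
- Delay 15%: equal steps 12.3/9.0/8.2; 225/450/225 23.2/14.5/12.3; 4 groups × 5 steps 15.4/9.6/8.2.

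The longer middle step keeps its advantage under delay. The four-group layout loses most of its own.

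**6. Patients for 80% power (CAC 1, ρ from near 0 to 0.20).** Equal steps about 2,350 to 3,190; 25/50/25 about 1,570 to 2,680; 4 groups × 5 steps about 1,560 to 2,290.

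**The case against.** The protocol gives no step lengths, and an article may leave them to the full protocol. A reader might infer that the plan uses three equal steps and so keeps two thirds of its patients out of the concurrent comparison. The document does not support that: equal steps are an assumption here, and step 2 may already be longer. Nor are steps 1 and 3 wasted, since they help to remove differences between centres. What stands is that only step 2 mixes the conditions, so its share needs to be set deliberately.

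The authors call the layout simple and pragmatic, which is a legitimate preference. A reader might infer that two groups is a mistake and that more switch dates are plainly better. That goes too far. Four groups over five steps leaves about 900/(16 × 5) = 11 patients per centre and step, and its advantage over equal steps falls to 0 to 3 points if uptake lags by 15% of trial time. Frequency of app use is itself a secondary outcome, so immediate uptake cannot be taken for granted.

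The stated design-effect check could be cited as an answer. However, 778 is exactly the unadjusted number, and checking a layout would not show that it is efficient.

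A reader might also take the two-clusters sentence to mean that only two units are randomised. The same section speaks of half of the centres and Setting of 16 centres, so that reading is not established. The ambiguity is a reason to state how the groups are formed.

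The figures above are, if anything, favourable. They use all 900 patients, although 900 includes the allowance for missing data, and a normal test with 16 clusters. With 778 evaluable patients the equal-step layout has 30 to 37% power (CAC 1).

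**Conclusion.** The point holds as a modest, inexpensive improvement. It is not an error in the choice of a stepped wedge. The protocol confines concurrent comparison to step 2. If steps are equal, power is about 34 to 38% at ICC 0.01 to 0.10 (26 to 37% at autocorrelation 0.8), against the intended 80%. Placing half of the enrolment in step 2 gives about 40 to 49% (30 to 48%). It was better than equal steps at every ICC and autocorrelation tried, and also in the delayed-uptake runs above. At ICC 0.10 and above the gain is small, about 2 to 6 points.

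The conclusion rests on adjustment for step, equal centre sizes and assumed correlations. A reader might infer that a better layout restores the planned power. It does not: the highest value in the table is about 57%, at ICC near 0.

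**What to change.** Keep the two groups, the two launch dates, 16 centres and 900 patients, and make these changes before centres are randomised:

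- State the step lengths and plan step 2 to hold about half of the enrolment, for example 225/450/225. With steady recruitment this means a middle step twice as long as each outer step.
- Randomise centres to the two groups stratified by setting (OFII or other), and reword the two-clusters sentence accordingly.
- Restate the power, or the sample size, for the layout adopted, with the ICC and autocorrelation assumed.

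The cost is shorter all-control and all-app steps: about 225/16 = 14 patients per centre in each, against 300/16 = 19 with equal steps. The numbers per condition do not change: 225 + 225 = 450 on the app and 450 on usual care, as with equal steps (150 + 300). Stretching step 2 much further is not useful: at ICC 0.10 and CAC 1, 20/60/20 gives 40.2% and 10/80/10 gives 35.3%, against 39.6%.

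More switch dates, such as four groups over five steps (about 51/45/44% at ICC 0.01/0.05/0.10), remain an option if logistics allow and uptake is expected to be rapid.

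### The randomised unit is inconsistent: the two clusters are defined as OFII and other structures, which taken literally makes rollout order the same thing as type of setting

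*Protocol article*

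**What the plan says.** Four statements in the protocol article bear on the unit of randomisation.

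- Justification of Analysis describes the design as one in which "clusters are randomized for the time at which the cluster will switch from the control condition to the intervention condition".
- Setting: "The study will be carried out in 16 centers taking care of and treating migrants". The centres are of several kinds: OFII immigration centres, PASS hospital consultations, nonprofit organisations and ambulatory professionals.
- Sample Size, on the rollout: "We will do a simple and pragmatic step wedge with 2 groups and 3 steps", with nobody exposed at the first step, then "second starting intervention for 1 group (half of the centers), and third all centers with the intervention".
- Sample Size, next sentence: "We plan to have 2 clusters with 450 participants in the OFII centers and 450 participants in the other structures".

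The article does not describe the 450/450 split as a quota or stratum. It does not say that allocation is stratified by setting, or that each rollout group mixes OFII and other centres. The Statistical Analysis section plans a mixed model without naming the random-effect unit. Screening structure is listed in Sample Size as a subgroup variable.

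**The concern.** If clusters are what is randomised and the two clusters are OFII and everything else, then OFII centres all switch at one time and all other centres at the other. The step-2 comparison, the only point at which exposed and unexposed centres are observed together, would then be between kinds of service as well as between app and no app. Justification of Analysis itself expects outside influences on screening, such as shifts in migration and pandemic behaviour. A residency check-up and a hospital or charity service need not respond to these in the same way.

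If instead the 16 centres are the clusters, the sentence about two clusters is wrong, and someone preparing the allocation list from this text could carry it out wrongly. Allocation cannot be redone once rollout has begun.

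**Working it through.** **The plan's own figure.** The inputs from Sample Size are 45% versus 55%, alpha 0.05 (taken as two-sided) and power 0.80. For two independent proportions with unpooled variance, n per arm = (1.96 + 0.8416)² × (0.45 × 0.55 + 0.55 × 0.45) / 0.10² = 388.5, rounded up to 389, so the total is 778. The stated 778 reproduces exactly as an individually randomised sample size. It contains no design effect, so it does not show whether 2 or 16 clusters were in mind. The article says that a design-effect check was made but gives no intracluster correlation or cluster count for it.

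**Number of possible rollout orders.** Two units, one per switch time, give 2 allocations, and in both the sequence is identical to setting type. Sixteen centres split 8:8 without restriction give C(16,8) = 12,870.

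**What the effect estimate compares under the literal reading.** Let group 1 switch at step 2 and group 2 at step 3. Exposure is (0, 1, 1) in group 1 and (0, 0, 1) in group 2. Subtracting row means (2/3, 1/3) and column means (0, 1/2, 1) and adding back the grand mean (1/2) leaves (−1/6, 1/3, −1/6) for group 1 and the negative for group 2. The sum of squares is 2 × (1/36 + 4/36 + 1/36) = 1/3. Dividing by it gives weights (−1/2, 1, −1/2), so with fixed group and step effects

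effect = [Y12 − (Y11 + Y13)/2] − [Y22 − (Y21 + Y23)/2],

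where the first index is the group and the second the step.

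**Bias from changes seen in OFII only.** OFII is taken as group 1; the sign reverses if it is group 2. The 5 points are an assumption for illustration. The target is the planned "increase this rate by 10%, from 45% to 55"%, that is, 10 points.

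| OFII-only change at steps 1, 2, 3 (points) | Bias (points) | Share of target |
|---|---|---|
| Constant difference (5, 5, 5) | 5 − 5 = 0 | 0 |
| Linear trend (0, 5, 10) | 5 − 5 = 0 | 0 |
| Lasting shift from step 2 (0, 5, 5) | 5 − 2.5 = 2.5 | 25% |
| Shift at step 3 only (0, 0, 5) | 0 − 2.5 = −2.5 | −25% |
| Confined to step 2 (0, 5, 0) | 5 − 0 = 5 | 50% |

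**If cluster is random and setting is not in the model.** A constant OFII-versus-other difference then leaks partly into the effect. With 2 clusters, 900/(2 × 3) = 150 participants per cluster and step, and a stable cluster effect, generalised least squares passes on 77% of the difference at an intracluster correlation of 0.001, 25% at 0.01, 6% at 0.05 and 3% at 0.10. These correlations are assumptions. The size of the difference is unknown, because the only screening rate given comes from one setting: "The overall rate of screening currently carried out as part of the STRADA study in OFII centers is around 45"%.

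**Information on between-cluster variation.** Two clusters over three steps give 6 cells. Intercept, cluster (1), step (2) and treatment (1) use 5 parameters and leave 1 degree of freedom. Sixteen centres over three steps give 48 cells. The same model uses 1 + 15 + 2 + 1 = 19 and leaves 29, if every centre recruits at every step.

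**Subgroup by screening structure.** Under the literal reading all OFII centres switch together, as do all the others. Within either setting there is no step at which some centres are exposed and others are not, so the subgroup estimate is a before-after comparison.

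**The case against.** The strongest reply is that the sentence is loose wording. The sentence before it defines the rollout in terms of groups of centres, and the disputed one uses a different word and divides the 900 participants by setting, which could simply be a recruitment split. It does not say which centres switch first. This is a fair reading, and it means the article does not establish that two units will be randomised. But nothing in the article says so, and Justification of Analysis attaches the randomisation to the very word used.

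It can also be said that randomisation of 16 individual centres is never stated. That is correct: it is inferred from Justification of Analysis, Setting and Sample Size together. The number of OFII centres is not given, and if it were 8, half of the centres and OFII could be the same set. That would remove the conflict over counts, but only by making the confounding real.

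A reader might infer that the literal reading leaves the app effect inseparable from any setting-specific change over time. The documents do not support that. Each setting contributes unexposed and exposed steps, and the table shows no bias for a constant difference or a linear trend. A reader might also attribute low power to the cluster wording. Any power figure needs an intracluster correlation and a cluster autocorrelation that the article does not give, so none is claimed here.

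**Conclusion.** The point stands as an inconsistency in the unit of randomisation, with a conditional consequence. That the passages do not agree is clear from the text. That rollout order will be confounded with setting follows only if the two-cluster sentence is carried out as written.

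In that case, with fixed group and step effects and an assumed 5-point change confined to OFII, the absolute bias runs from zero (constant or linear) through 2.5 points (a lasting shift) to 5 points (step 2 only), against a target of 10. It scales in proportion to the assumed change. Almost no information on between-cluster variation would remain, and the setting subgroups would have no concurrent control. This should be settled before the allocation list is drawn up.

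**What to change.** In Sample Size and Setting, state that the centre is the cluster and the unit of randomisation. Allocate the 16 centres to the two switch times with stratification by setting (OFII versus other), as evenly as the centre counts allow. Replace the two-cluster wording by two recruitment strata with a target of 450 participants each. In Statistical Analysis, name a random effect for centre and a fixed effect for setting alongside step and treatment.

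The cost is a few sentences and a stratified allocation list, with no extra participants. The change does not settle whether 778 or 900 participants suffice for a stepped wedge design, which is a separate question.
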